##### Operation duration

This is the duration in hours of the appendicectomies performed in rural and metropolitan hospitals. This again will provide general information about the complexity of cases performed.

##### Rate of negative appendicectomy

This is the rate of appendicectomies performed in normal appendices. This is reported on the case report forms under macroscopic and microscopic appearance, as a normal appendix or simple or complex appendicitis. This will allow us to compare the rates of negative appendicectomies between rural and metropolitan hospitals and provide us with data to examine the potential reasons behind this, outlined in the “Introduction” section.

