## Introduction

Surgery wait times after diagnosis of appendicitis are an important factor influencing the success of a patient’s treatment. Clinical evaluation in conjunction with the Alvarado or appendicitis inflammatory response scores is used to determine the risk of appendicitis in symptomatic patients. A large cohort study has shown that, in cases of uncomplicated appendicitis, short delays to operation of < 24 h do not increase the rates of complex appendicitis [1]. This finding was confirmed in a meta-analysis of 11 non-randomized studies, where a short in-hospital delay of 12 to 24 h before surgery did not increase the risk of complex appendicitis including perforation. However, delaying appendicectomy for > 48 h was associated with increased surgical site infections and other complications [2]. A laparoscopic appendicectomy approach should be performed unless contraindicated [3].

Negative appendicectomy refers to surgical removal of the normal appendix on final pathological report [4]. The Second Australian Atlas of Healthcare Variation in 2017 revealed that negative appendicectomy rates in Australia were 21–24% [5]. With appendicectomies carrying many risks such as possible wound infection or rupture, intestinal injury, postoperative abdominal abscess, or urinary infections, unnecessary appendicectomy can have significant impacts [6]. A recent audit conducted to examine pediatric negative appendicectomy rates at Southwest Health Campus Bunbury including 421 patients found the negative appendicectomy rate to be higher than observed in previous literature at 45.58%. The authors noted this was concerning since diagnostic laparoscopy in children is not benign, with negative appendicectomy having a similar morbidity risk to appendicectomy for uncomplicated appendicitis [7].

The proposed study will be a quantitative multicenter retrospective cohort design with the primary aim of assessing the difference between appendicectomy wait times between rural and urban hospitals in Western Australia and the effect of this on selected outcome measures. The secondary aim is to compare the rates of negative appendicectomies between these hospitals.

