It is hypothesized that there will be a higher rate of negative appendicectomies in rural hospitals as opposed to metropolitan hospitals, rooting from various potential factors. According to an audit examining the rural–urban differences in surgical interventions in the United States (US), there were higher rates of an array of surgeries including appendicectomies in areas classified rural according to US standards. This was contrary to the authors’ hypothesis that rurally located patients would have lower surgical rates. The authors proposed this could be explained by rural patients experiencing overall poorer health, increasing the indications for many surgeries to be undertaken [8]. This can be extrapolated to the Australian setting, where, according to the Australian Institute of Health and Welfare (AIHW), risk factors such as smoking, obesity, and hypertension amongst many others all increased with rurality, as well as chronic health conditions and burden of disease [9]. Another factor which may contribute to potential higher negative appendicectomies is that doctors may have a lower threshold to perform the surgery in order to avoid potential severe complications, such as perforation in a setting where there is reduced healthcare access. This may in turn lead to reduced surgical wait times in rural settings, addressing both our primary and secondary outcomes. Another US study on pediatric patients revealed that rural hospitals were 50% more likely to perform negative appendicectomies. The authors explained this is due to negative appendicectomies being justified in order to “decrease delay in diagnosis and subsequently lower the risk of appendiceal perforation” [10]. The authors noted that this disparity may also be in part due to reduced access to pre-operative imaging such as computed tomography to make the diagnosis. It is suspected a combination of all stated factors may play a role in reduced surgical wait times and negative appendicectomies in rural compared to metropolitan hospitals in Western Australia.

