## Methods

This protocol adheres to the reporting recommendations relevant specifically to an observational retrospective cohort study of the Guidelines for Reporting Outcomes in Trial Protocols: The SPIRIT-Outcomes (2022), obtained via the Equator Guidelines [12]. Consultation with doctors in the field of general surgery and rural health experts from WACHS was performed in the development of this protocol to ensure that the needs of rural populations are not misrepresented.

The study design was chosen to be retrospective due to the difficulties of prospective recruitment by medical student data collectors for whom it is unrealistic to conduct a prospective study to recruit appendicitis patients due to the transient nature of placements, especially in large metro hospitals, which would likely lead to selection bias (for more details, see “Collaborative teams”). Four separate 2-week data collection periods were preferred over one asynchronous period of data collection to provide structure for the data collection into four 6-month retrospective review periods which would allow more medical students to participate in data collection in the project overall if each student is allocated one data collection period and to divide the amount of retrospective data to be reviewed into a manageable amount for each mini-team (for more details see “Collaborative teams”).

The retrospective time period which will be examined for eligible patients and from which data is collected will be over a 2-year period from January 2022 to November 2023. Appendicectomy patients will be identified from the operating room register by members of the mini-teams discussed in the “Methods” section, expected to be mainly medical student data collectors currently on placement at the relevant hospital, and then, each respective hospital’s emergency room data collection subsequently will be accessed to fill out the case report forms. The data will be collated via case report forms based on demographics and clinical findings, pre-operative investigations, and management and follow-up. Case report forms with > 95% completeness will be accepted for pooled analysis. The expected duration of retrospective data collection will be 8 months. This includes the four 2-week data collection periods.

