### Data analysis

Normally distributed data will be reported as mean (standard deviation (SD)), and non-normally distributed data will be reported as median (interquartile range (IQR)). Independent *t*-tests or ANOVAs will be used for normally distributed variables, Mann–Whitney *U* and Kruskal–Wallis tests will be used for non-normally distributed continuous or ordinal variables, and chi-squared tests will be used for categorical variable comparisons. When comparing appendicectomy wait times with complication incidence during the data analysis phase, a *P* value of 0.05 will be used to determine statistical significance. There will be no interim analysis or audit planned due to the grouping of data sets over four data collection periods. As this is a retrospective observational cohort study, there are no plans to deviate from the original protocol statistical plan or study design.

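### The rural–metropolitan comparison of negative-appendicectomy rates is fixed as an unadjusted chi-squared test, so a case-mix difference could create or hide a rural difference whose reasons the study means to examine

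*Protocol article*

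**What the plan says.** Comparing negative-appendicectomy rates between rural and metropolitan hospitals is the stated secondary aim (Abstract and Introduction). It carries a directional hypothesis: "It is hypothesized that there will be a higher rate of negative appendicectomies in rural hospitals as opposed to metropolitan hospitals". Under Rate of negative appendicectomy the protocol says "This will allow us to compare the rates of negative appendicectomies between rural and metropolitan hospitals", and adds that the data will be used to look into the explanations given in the Introduction.

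Those explanations are of two kinds. Some concern the patients: smoking, obesity, hypertension and chronic disease are said to increase with rurality. Others concern the service: a lower threshold to operate and less access to preoperative imaging.

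The Data analysis section states that "chi-squared tests will be used for categorical variable comparisons". Its other named methods are t-tests, ANOVA, Mann–Whitney and Kruskal–Wallis. No adjusted or stratified analysis is mentioned, and the section closes by saying that "there are no plans to deviate from the original protocol statistical plan or study design". The forms are described in Methods as "case report forms based on demographics and clinical findings, pre-operative investigations, and management and follow-up".

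**The concern.** Whether an appendix was normal is a categorical outcome, so by the stated rule its comparison is a two-by-two chi-squared test. Region is defined by which health service runs the hospital, not by allocation. If rural and metropolitan sites treat a different mix of patients, the crude difference combines that mix with any difference in operating threshold or diagnostic access. The test cannot tell them apart. The mix could inflate a difference, produce one where none exists, or conceal a real one.

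This matters because the protocol does not stop at describing two rates. It wants to say something about reasons, and its own list of reasons mixes patient characteristics with features of the service. What is at stake is the interpretation of the secondary aim. The crude rates themselves remain valid as description.

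**Working it through.** **1. Sample size from the Sample size section.** Metropolitan: 4 × 350 = 1400. Rural: 5 × 50 = 250. Total 1650. The claims-based route gives 2 × 818 = 1636. Both agree with the stated total of over 1600, so the split of 1400 to 250 is used below.

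**2. What the crude test can detect.** The level of 0.05 is stated only for wait time against complications ("value of 0.05 will be used to determine statistical significance"). It is assumed here to apply two-sided. With a metropolitan rate of 21% to 24%, the national range in the Introduction, an observed difference of about 5.6 to 5.9 points reaches P < 0.05. A true difference of about 8.2 to 8.6 points has 80% power. A spurious shift of a few points is therefore not trivial beside the effects the study can see.

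**3. Illustration with no true rural effect.** The documents give no negative rate by age or sex for patients aged 16 or older, and no case mix by region. All of the following are assumptions:
- two strata with the same rates in both regions: a = 35%, b = 20% or 24%
- share in the higher-rate stratum: s = 25% metropolitan, s + x rural, with x = 5, 10 or 20 points.

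Expected crude rates: p_M = s·a + (1 − s)·b and p_R = (s + x)·a + (1 − s − x)·b. The spurious difference is d = x·(a − b).

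Rejection probability: 1 − Φ[(1.96·SE0 − d)/SE1] + Φ[(−1.96·SE0 − d)/SE1]. SE0 is the pooled and SE1 the unpooled standard error at 1400 and 250. This is the chi-squared test without continuity correction, treating patients as independent.

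| a v b | x | p_M | p_R | d (points) | crude rejection |
|---|---|---|---|---|---|
| 35% v 24% | 5 | 26.75% | 27.30% | 0.55 | 5.5% |
| 35% v 24% | 10 | 26.75% | 27.85% | 1.1 | 6.7% |
| 35% v 24% | 20 | 26.75% | 28.95% | 2.2 | 11.6% |
| 35% v 20% | 5 | 23.75% | 24.50% | 0.75 | 5.9% |
| 35% v 20% | 10 | 23.75% | 25.25% | 1.5 | 8.4% |
| 35% v 20% | 20 | 23.75% | 26.75% | 3.0 | 18.2% |

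Last row in full: SE0 = 0.0294 and SE1 = 0.0302, so (1.96 × 0.0294 − 0.030)/0.0302 = 0.915 and (−1.96 × 0.0294 − 0.030)/0.0302 = −2.90. The upper tail is 0.180 and the lower 0.002, together 0.182. Reversing the sign of x shifts the crude difference the other way by the same amount, with similar rejection (17.0% at x = −20, 35% v 20%).

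**4. Sensitivity.** A weaker gradient of 30% v 24%, with the same shares, gives 5.2% to 7.1%. A stronger one of 35% v 15%, with half of metropolitan patients in the higher-rate stratum and 30 points more at rural sites, gives about 51%. In simulations with this 35% v 15% contrast and with 30% v 15% and 30% v 20%, a stratified Mantel–Haenszel test stayed near 5%. That return to 5% holds by construction, because the simulated patients are independent and the only confounder is known and measured.

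**5. Clustering.** Nine hospitals supply the data and region is a hospital-level factor. With an assumed intra-hospital correlation ρ and no mix difference, the variance of the rate difference is multiplied by [(1 + 349ρ)/1400 + (1 + 49ρ)/250] / [1/1400 + 1/250]. That is 1.47 at ρ = 0.005 and 2.89 at ρ = 0.02. The crude test then rejects in about 11% and 25% of studies. Adjusting for age and sex alone would leave this untouched.

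**The case against.** The strongest reply is that the aim is only to compare rates, in a study framed partly as an audit with standards. For that purpose crude rates are legitimate, and if they truly differ, a significant result is not a false positive. The explanatory language is also cautious: the Introduction speaks of factors that may contribute. This stands for the descriptive comparison. It does not cover the stated intention to examine reasons, which a two-by-two table cannot serve.

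Another reply is that adjustment may be left to a separate analysis plan. The article, however, names its tests and says it will not depart from them, so the comment concerns a stated method.

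Two stronger readings are tempting, and the documents support neither.

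- A reader might infer that the protocol's own figures show the negative rate varying with age, because a paediatric audit "found the negative appendicectomy rate to be higher than observed in previous literature at 45.58" per cent while "negative appendicectomy rates in Australia were 21–24" per cent. The audit was done at Bunbury, one of the study's rural sites, and is set against a national figure, so age, site and rurality cannot be separated. Under-16s are also excluded from this cohort, and no rate by sex is given. The 45.58% is therefore not used in the illustration.
- A reader might infer that the suggestions on preoperative practice foreseen in the Aim section rest on the rural–metropolitan difference. That section ties them to reducing the incidence of negative appendicectomy, not to the contrast between regions.

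It is also fair to say that age and sex adjustment would not remove every patient difference the Introduction lists, and that the form is described only as holding demographics, without naming items.

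**Conclusion.** The point holds in a limited form. The protocol fixes an unadjusted test for a non-randomised comparison, expects patient risk factors to differ by rurality, and means to examine reasons for any difference. Case mix could create or hide a rural–metropolitan difference, and neither its size nor its direction can be derived from the documents.

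Under the main assumptions above, the spurious difference is about 0.6 to 3 points and the crude test rejects in about 5.5% to 18% of studies instead of 5%. At the low end that is negligible. It shows what a case-mix difference could do and does not predict what will happen. This deserves correction before analysis, but it does not undermine the study: it affects how the secondary aim is interpreted, not whether the crude rates can be reported.

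**What to change.** In the Data analysis section, keep the crude rates and add:
- A binomial (logistic) model for negative appendicectomy with rural/metropolitan, age and sex, as recorded under demographics. Report it as an adjusted risk difference with a 95% confidence interval.
- Standard errors that allow for clustering by hospital. Region is constant within hospital, so hospital cannot enter as a fixed effect beside it. With nine hospitals a small-sample correction is needed.
- A statement that preoperative imaging is left out of this main model, because the Introduction names it as a possible cause of the difference.
- A statement that anything said about reasons for a rural difference rests on the adjusted estimate, with the remaining unmeasured patient differences acknowledged.

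The cost is some wording, one extra model and a possibly wider interval. At 21% to 24% of 1650, about 347 to 396 negative appendicectomies are expected, enough for a model of this size. No new data are needed if age and sex are among the demographics on the form, which should be confirmed.

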## Methods

This protocol adheres to the reporting recommendations relevant specifically to an observational retrospective cohort study of the Guidelines for Reporting Outcomes in Trial Protocols: The SPIRIT-Outcomes (2022), obtained via the Equator Guidelines [12]. Consultation with doctors in the field of general surgery and rural health experts from WACHS was performed in the development of this protocol to ensure that the needs of rural populations are not misrepresented.

The study design was chosen to be retrospective due to the difficulties of prospective recruitment by medical student data collectors for whom it is unrealistic to conduct a prospective study to recruit appendicitis patients due to the transient nature of placements, especially in large metro hospitals, which would likely lead to selection bias (for more details, see “Collaborative teams”). Four separate 2-week data collection periods were preferred over one asynchronous period of data collection to provide structure for the data collection into four 6-month retrospective review periods which would allow more medical students to participate in data collection in the project overall if each student is allocated one data collection period and to divide the amount of retrospective data to be reviewed into a manageable amount for each mini-team (for more details see “Collaborative teams”).

The retrospective time period which will be examined for eligible patients and from which data is collected will be over a 2-year period from January 2022 to November 2023. Appendicectomy patients will be identified from the operating room register by members of the mini-teams discussed in the “Methods” section, expected to be mainly medical student data collectors currently on placement at the relevant hospital, and then, each respective hospital’s emergency room data collection subsequently will be accessed to fill out the case report forms. The data will be collated via case report forms based on demographics and clinical findings, pre-operative investigations, and management and follow-up. Case report forms with > 95% completeness will be accepted for pooled analysis. The expected duration of retrospective data collection will be 8 months. This includes the four 2-week data collection periods.

The planned first data collection period will only record information for eligible patients receiving appendicectomy at the relevant center between January and June 2022 retrospectively to their surgeries being performed, and then, a check of the patient’s record until the 30-day postoperative interval on the same data collection source will be conducted to record any readmissions or complications.

The planned second data collection period will only record information for eligible patients receiving appendicectomy at the relevant center between June 2022 and December 2022 retrospectively to their surgeries being performed, and then, a check of the patient’s record until the 30-day postoperative interval on the same data collection source will be conducted to record any readmissions or complications.

The planned third data collection period will only record information for eligible patients receiving appendicectomy at the relevant center between January 2023 and June 2023 retrospectively to their surgeries being performed, and then, a check of the patient’s record until the 30-day postoperative interval on the same data collection source will be conducted to record any readmissions or complications.

The planned fourth data collection period will only record information for eligible patients receiving appendicectomy at the relevant center between June 2023 and November 2023 retrospectively to their surgeries being performed, and then, a check of the patient’s record until the 30-day postoperative interval on the same data collection source will be conducted to record any readmissions or complications.

For the purpose of this project, sites under WA Country Health Service (WACHS) jurisdiction will be considered rural, that is, Albany Hospital, Bunbury Hospital, Broome Health Campus, Geraldton Hospital, and Hedland Health Campus. The other sites (Royal Perth Hospital, Sir Charles Gairdner Hospital, Fiona Stanley Hospital, Armadale Health Service) will be considered urban.

Following data collection, only case report forms with > 95% data completeness will be accepted for pooled analysis. Centers with > 5% missing data points will be excluded and collaborators from those centers withdrawn from the published list of citable collaborators. This is in order to provide some leeway for potential missing data, while also acknowledging that case report forms with ≥ 5% missing data may not be useful for our purposes. As the data originates from emergency department records, there is no perceived risk of including false or unused data. This study RGS6483 has received HREC approval by the Royal Perth Hospital HREC Ethics Committee, with a waiver of consent obtained and the HREC was notified of amendments to the protocol made on April 21, 2024.

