## Aim

The aim of this study was to determine the variation in appendicectomy surgery wait times between rural and urban areas in Western Australia after initial presentation and diagnosis at an emergency department. Within these populations, selected outcome measures will be examined by time from:Initial presentation for the presenting complaint at an emergency department to the patient being seen by a general surgery registrar or consultant.Time from patient being seen by a general surgery registrar or consultant to surgery being performed.

The reason for taking data based on the two separate time frames is that by recording time between initial emergency department presentation to the patient being seen by the general surgery registrar or consultant, it will be possible to account for those patients who are not immediately diagnosed and then go on to have a delayed diagnostic laparoscopy and appendicectomy and evaluate and measure the magnitude of outcome impacts that an increased duration of this time could produce. Furthermore, the case report forms collect data on previous presentations of the same presenting complaint within the past week to capture any *prior premature discharge from the same site on initial evaluation of presenting complaint*.

This will allow examination of the effect of both triage wait times and timing of surgery after diagnosis on perforation, operation duration, and length of stay amongst each of the subpopulations.

Additionally, it is hoped to establish the rate of negative appendicectomies in urban and rural areas in Western Australia and if necessary make suggestions preoperatively to reduce their incidence.

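### The 30-day complication check reads only the operating hospital's source, so events managed elsewhere go unrecorded, possibly unequally by rurality; the effect on the wait-time test is conditional and modest

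*Protocol article*

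**What the plan says.** Methods in the protocol article finds cases in the operating room register and then states that "each respective hospital’s emergency room data collection subsequently will be accessed to fill out the case report forms". For every review window, follow-up is a look at the patient's record up to the "30-day postoperative interval on the same data collection source will be conducted to record any readmissions or complications". The unit is the operating centre: the first window, for instance, covers "eligible patients receiving appendicectomy at the relevant center between January and June 2022". Under Aim, earlier presentations are likewise sought only to detect "prior premature discharge from the same site on initial evaluation of presenting complaint".

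Two statements on data quality bear on this. Methods says that "only case report forms with > 95% data completeness will be accepted for pooled analysis", and also that "As the data originates from emergency department records, there is no perceived risk of including false or unused data".

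Under Data analysis, the only comparison given its own significance level (0.05) is introduced by the words "When comparing appendicectomy wait times with complication incidence during the data analysis phase". The tests named there are unadjusted. Complications and readmissions do not appear among the primary and secondary outcome measures.

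**The concern.** An event that never enters the one source searched cannot be recorded. A patient who goes to another hospital with a wound infection looks the same on the form as a patient who recovers without trouble. The completeness filter cannot tell them apart, because it counts blank fields and a recorded absence of complications is not blank. The assurance about false data does not consider missed events.

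Where a patient re-presents plausibly depends on distance and access to care, and the study compares hospitals by location. The Introduction itself refers to poorer access in rural settings. Capture could therefore vary with the exposure. A rural-urban difference in complications could then be created or hidden by where patients seek care. Some of that distortion could pass into the wait-time test if rural and urban waits also differ.

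**Working it through.** **Group sizes (Sample size section).** 818 claims a year × 2 = 1636, which agrees with the stated figure of over 1600. The per-site figures give 4 × 350 = 1400 urban and 5 × 50 = 250 rural, 1650 in all, so rural patients are 250/1650 = 15%. The calculations use 1400 and 250.

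**Assumptions (the article gives none of these).** The true 30-day event risk is 10% everywhere and waiting has no effect. Capture depends only on site type. The share of patients with a delayed operation is 50% urban and 30% rural (mild gap) or 60% and 20% (wide gap); shorter rural waits follow the Introduction's hypothesis.

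**Rural-urban contrast.** Observed risk = true risk × capture, so observed risk ratio = rural capture / urban capture. At 90% urban and 70% rural: 7.0% / 9.0% = 0.78.

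**Wait-time test.** Pool both site types and compare delayed with not delayed. Wide gap, 90/70:
- Delayed: 1400 × 0.6 + 250 × 0.2 = 840 + 50 = 890 patients; risk (840 × 0.09 + 50 × 0.07)/890 = 79.1/890 = 8.89%.
- Not delayed: 560 + 200 = 760 patients; risk (560 × 0.09 + 200 × 0.07)/760 = 64.4/760 = 8.47%.
- Risk ratio 1.05.

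The true risk cancels from these ratios, so they do not depend on the 10% assumption. The false-positive rates do. They are the rejection probability of the two-proportion z-test with pooled standard error, two-sided 0.05 (sidedness is not stated in the article).

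| Capture urban/rural | Rural-urban RR | Wait-time RR, mild / wide gap | False positives, wait-time test, mild / wide |
|---|---|---|---|
| 70/70 | 1.00 | 1.00 / 1.00 | 5.0% / 5.0% |
| 90/70 | 0.78 | 1.02 / 1.05 | 5.3% / 6.0% |
| 70/90 | 1.29 | 0.97 / 0.94 | 5.3% / 6.2% |
| 90/50 | 0.56 | 1.05 / 1.10 | 6.1% / 9.2% |
| 50/90 | 1.80 | 0.93 / 0.86 | 6.5% / 11.4% |

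If the delayed share is the same in both site types, the wait-time risk ratio is 1.00 and the false-positive rate 5.0% in every row. For true risks of 5% to 15%, the wait-time false-positive rate in the unequal-capture rows with a wait gap runs from 5.1% to 14.9%.

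**Stratifying.** Within one site type, delayed and non-delayed patients have the same captured risk (for example 7.0% / 7.0% among rural patients at 90/70), so the stratum risk ratio is 1.00. Stratification removes the bias as long as capture does not also depend on waiting within a stratum.

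**Equal under-capture.** This leaves the null test valid but costs power. For a true 10% v 15% with 825 per group, power is 87% at full capture, 83% at 90%, 71% at 70% and 56% at 50%.

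**The case against.** The strongest reply is that the large numbers belong to a comparison the plan does not specify. Data analysis names wait time against complications; a rural-urban complication contrast is not among the listed outcomes. At 90/70 capture the named test barely moves, and without a rural-urban difference in waits it does not move at all. That stands, and it limits the size of the point. It does not remove it: the Abstract promises the effect of rural-urban wait differences on operative outcomes, so readers are likely to read complication results by site type.

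Three stronger readings are tempting and are not supported.
- A reader might infer that missed events are scored as no event. The article gives no coding rule and the case report form is not shown. What is established is that such events cannot be recorded from the source described.
- A reader might infer that only emergency department attendances are searched, so that direct ward readmissions are lost too. The forms also need histology, operation duration and length of stay, which an emergency department dataset alone is unlikely to hold. A source limited to the operating hospital is the likelier reading; a source limited to its emergency department is not established.
- A reader might infer that differential misclassification in a known direction is shown. No capture figures are given, either group could re-present elsewhere more often, and capture could be equal.

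**Conclusion.** The point holds in a limited form. As written, 30-day complications and readmissions are those visible at the operating hospital, and nothing in the article adds another source or detects what is missed. A rural-urban contrast of these events could be materially biased: risk ratio 0.78 or 1.29 at a 90/70 split and 0.56 or 1.80 at 90/50, with no true difference. The wait-time test is biased only if waits differ by rurality, and then modestly, because rural patients are about 15% of the sample. All capture and delay shares are assumptions. It would be wrong to conclude that the primary result is compromised: wait time, laparoscopic and complex appendicitis rates, hospital stay, operation duration and negative appendicectomy do not use the 30-day check. The change is worth making because it is cheap and settles what the study may claim about complications.

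**What to change.** - State which records the 30-day check covers. If the source does show other hospitals' encounters, one sentence saying so resolves most of the point.
- Otherwise define the outcome as 30-day complication, re-presentation or readmission recorded at the operating hospital, and list it under secondary outcome measures. Code absence as no record at this site, not as no event, and do not report it as a total complication rate.
- Stratify or adjust the wait-time test by site or rurality.
- Add a sensitivity table that divides the observed risks by assumed capture of 60% to 100% in each group. Its corners correspond to rural-urban capture ratios of 0.60 (60/100) and 1.67 (100/60).
- Report complications up to index discharge only as a supplementary outcome. It does not depend on where patients re-present, but its window varies with length of stay, itself a study outcome, and it misses infections that appear after discharge.

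The cost is protocol wording, one form code, a stratified or adjusted analysis and one table. The downside is slightly more analysis and a narrower claim about complications. No record linkage is needed.
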